### Statistical Methods

#### Evaluation of Efficacy

We will also examine the descriptive statistics for the participants’ baseline characteristics and compare them across the 3 study groups. The main analysis will be performed based on the ITT principle, involving all the randomized participants to investigate the effectiveness of the interventions. The ITT principle can minimize potential bias owing to dropouts and can be applied while performing further preprotocol analyses. The effects of the interventions on the primary outcome (eg, vaccination intention) and secondary outcomes (ie, knowledge related to COVID-19 vaccines, decisional conflict, psychological stress related to vaccination, perceived benefits of COVID-19 vaccines, and perceived barriers to COVID-19 vaccines) will be estimated using linear mixed-effects models for continuous outcome variables and generalized linear mixed-effects models for categorical outcome variables. The test statistic will be calculated to assess any significant intervention benefit; we will use 2-sided *P* values with α=.05 to calculate the level of significance.

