#### Subanalyses

We will perform a path analysis to examine the theoretical constructs as potential mediators following the effect evaluation. For each outcome, a path analysis will be performed to describe the direct and indirect relationships, including the perceived benefits of and barriers to the COVID-19 vaccine. Path models are statistical methods that, compared with multiple regressions, allow for the simultaneous assessment of several regression paths occurring between multiple dependent and independent variables and for the computation of direct, indirect (mediated), and total effects. Standardized parameter estimates (standardized β) will be used to compare the magnitude of associations between media use and mediators. The model parameters and SE estimates are to be calculated. The participants with missing data will be excluded from analysis. Statistical analyses will be conducted using STATA (version 15; StataCorp LLC), SAS (version 9.4; SAS Institute), and R (version 4.2; R Foundation for Statistical Computing) software.

In addition, we will conduct subgroup analyses according to the preintervention intent for vaccination. We will observe how the degree of vaccination intention changes in the 2 groups. Among those who have already been willing to receive a COVID-19 vaccine, there are cases in which their decisions are passive or involuntary owing to social pressure or economic activity. Therefore, we seek to identify whether the nature of their decisions changes through the intervention.

The Data Monitoring Committee comprises the Principal Investigator, independent external data managers, and statisticians. The committee is responsible for data quality throughout the data collection, analysis, and reporting processes. The Data Monitoring Committee is independent of the research funding agency and has no competing interests.

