## Results

Data were collected from December 2021 to January 2022. This paper was initially submitted before data analysis began. The results are expected to be published in the winter of 2023.

The number of individuals who initially expressed their intention to participate was 1066. Of these 1066 individuals, 515 (48.31%) people participated in the first survey, excluding 551 (51.69%) people who did not meet the inclusion criteria. All dropouts were individuals without underlying diseases. Of the 515 participants in the first survey, 466 (90.5%) participated in all 3 rounds and 69 (13.4%) dropped out. No significant differences were observed in sex, age group, residence area, education level, marital status, or willingness to receive a COVID-19 vaccine between those who participated in all 3 surveys and those who dropped out based on the first survey (Table 3). The results of the chi-square test conducted to confirm the distribution bias of the participants assigned to the intervention groups (SMART-DA and SMART-DA-a) and those assigned to the control group, in terms of sex, age group, region of residence, education, marital status, and intention to receive a COVID-19 vaccine, showed that no significant differences were observed (Table 4). Among the 515 individuals who completed the first survey, 294 (57.1%) were male and 221 (42.9%) were female, and the age distribution was even (18-29 years, n=90, 17.5%; 30-39 years, n=98, 19%; 40-49 years, n=124, 24.1%; 50-59 years, n=123, 23.9%; 60-69 years, n=80, 15.5%). The rate of college education or higher (418/515, 81.2%) was higher than that of high school graduation (97/515, 18.8%), and the most common marital status was having a spouse (310/515, 60.2%). The proportion of those who responded that they had low or no intention of receiving a COVID-19 vaccine was 46% (237/515), and the proportion of those who responded that they had high intention of receiving a COVID-19 vaccine was 53.9% (278/515), indicated a rather high initial willingness among the participants to receive a COVID-19 vaccine.

**Table 3 table3:** Comparison of the participants who responded 3 times with those who responded <3 times (N=515).

			Incomplete response (<3 times; n=69), n (%)		Full response (3 times; n=446), n (%)		*P* value	
**Sex**								.10
	Male	33 (47.8)		261 (58.5)				
	Female	36 (52.2)		185 (41.5)				
**Age (years)**								.37
	18-29	10 (14.5)		80 (17.9)				
	30-39	12 (17.4)		86 (19.3)				

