	40-49	16 (23.2)		108 (24.2)				
	50-59	23 (33.3)		100 (22.42)				
	≥60	8 (11.6)		72 (16.1)				
**Residence**								.53
	Urban	66 (95.7)		418 (93.7)				
	Rural	3 (4.3)		28 (6.3)				
**Education**								.81
	High school graduation or lower	11 (15.9)		86 (19.3)				
	College and above	58 (84.1)		360 (80.7)				
**Marital status**								.92
	Other (unmarried, widowed, or divorced)	26 (37.7)		179 (40.1)				
	With a spouse	43 (62.3)		267 (59.9)				
**Willingness to receive a COVID-19 vaccine**								.17
	Low	37 (53.6)		200 (44.8)				
	High	32 (46.4)		246 (55.2)				

**Table 4 table4:** Basic characteristics of the participants at baseline (N=515).

			Total, n (%)		SMART-DA group (n=172), n (%)		SMART-DA-α group (n=172), n (%)		Control group (n=171), n (%)		*P* value	
**Sex**												.99
	Male	294 (57.1)		99 (57.6)		98 (57)		97 (56.7)				
	Female	221 (42.9)		73 (42.4)		74 (43)		74 (43.3)				
**Age (years)**												.93
	18-29	90 (17.5)		26 (15.1)		32 (18.6)		32 (18.7)				
	30-39	98 (19)		38 (22.1)		29 (16.9)		31 (18.1)				
	40-49	124 (24.1)		42 (24.4)		41 (23.8)		41 (24)				
	50-59	123 (23.9)		40 (23.3)		45 (26.2)		38 (22.2)				
	≥60	80 (15.5)		26 (15.1)		25 (14.5)		29 (17)				
**Residence**												.29
	Urban	484 (94)		162 (94.2)		158 (91.9)		164 (95.9)				
	Rural	31 (6)		10 (5.8)		14 (8.1)		7 (4.1)				
**Education**												.73
	High school graduation or lower	97 (18.8)		34 (19.8)		35 (20.3)		28 (16.4)				
	College and above	418 (81.2)		138 (80.2)		137 (79.7)		143 (83.6)				
**Marital status**												.57
	Other (unmarried, widowed, or divorced)	205 (39.8)		70 (40.7)		67 (39)		68 (39.8)				
	With a spouse	310 (60.2)		102 (59.3)		105 (61)		103 (60.2)				
**Willingness to receive a COVID-19 vaccine**												.99
	Low	237 (46)		79 (45.9)		80 (46.5)		78 (45.6)				
	High	278 (54)		93 (54.1)		92 (53.5)		93 (54.4)				

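### The missing-data exclusion rule has no stated scope and, as worded, conflicts with the intention-to-treat analysis of everyone randomised

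*Protocol article*

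**What the plan says.** Two statements in the Statistical Methods of the protocol article bear on who is analysed.

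- Evaluation of Efficacy: "The main analysis will be performed based on the ITT principle, involving all the randomized participants to investigate the effectiveness of the interventions". The models named there are "linear mixed-effects models for continuous outcome variables and generalized linear mixed-effects models for categorical outcome variables".
- Subanalyses, in the paragraph on path analysis: "The participants with missing data will be excluded from analysis". The sentence before it concerns estimates from the path models. The sentence after it is general: "Statistical analyses will be conducted using STATA (version 15; StataCorp LLC), SAS (version 9.4; SAS Institute), and R (version 4.2" and so on.

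The article gives no other rule for missing data. The Results then report the attrition: "Of the 515 participants in the first survey, 466 (90.5%) participated in all 3 rounds and 69 (13.4%) dropped out". Table 3 compares incomplete with full responders on six baseline variables, and the text concludes: "No significant differences were observed in sex, age group, residence area, education level, marital status, or willingness to receive a COVID-19 vaccine".

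**The concern.** The exclusion sentence names no analysis. It stands between a sentence about path models and a sentence about all the software, so it can be read either way. Sample Size and Power gives the wider reading some support, because it sizes the trial on an analytic sample of 450 that remains after dropout.

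The two readings have different consequences.

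- **Rule applies to the main analysis.** The primary comparison becomes a complete-case analysis under an intention-to-treat label. People are removed because of what happened after randomisation, and the arm contrast is biased if those who leave differ between arms.
- **Rule applies only to the path analysis.** The direct and indirect effects are estimated in a selected subset, while the total effect is estimated in everyone. The two need not agree.

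Two analysts following the text in good faith could report the primary outcome on 515 or on 446 people, and the text would not settle which is right.

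**Working it through.** **Inputs**

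- Randomised: Study Design says that those who complete the baseline survey are randomised. Table 4 is titled "Basic characteristics of the participants at baseline (N=515") and gives arms of 172, 172 and 171, which sum to 515.
- Incomplete responders (fewer than three surveys): 69 (Table 3).
- Full responders: Table 3 heads the column "Full response (3 times; n=446), n" (%). The text says 466, but 466 + 69 = 535, whereas 446 + 69 = 515. I use 446.
- Low willingness at baseline: 37 of 69 incomplete and 200 of 446 full responders (Table 3).
- Significance level: two-sided 0.05 (Evaluation of Efficacy).

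**1. The article's own figures**

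69/515 = 13.4%, as stated. A Pearson chi-square without continuity correction on the willingness counts gives P = .173, against .17 in Table 3.

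**2. Size of the loss if any missing survey leads to exclusion**

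- Remaining: 515 - 69 = 446, and 446/515 = 86.6%.
- Standard error ratio: sqrt(515/446) = 1.075, so about 7.5% larger.

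Both are ceilings. The 69 include anyone with one or two surveys, and the split is not given. People with a baseline survey only add little to a post-baseline contrast even when they are kept, so the precision that can be recovered is less than 7.5%.

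**3. What Table 3 can show about willingness**

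- Low willingness: 37/69 = 53.6% against 200/446 = 44.8%, a gap of 8.8 points.
- Standard error: sqrt(0.536 × 0.464/69 + 0.448 × 0.552/446) = 0.0645.
- 95% CI: 8.8 ± 1.96 × 6.45, that is -3.9 to 21.4 points.
- Power of a two-sided 5% test with 69 and 446: about 27% for the observed gap, 34% for 10 points, and 80% only at about 18 points.
- Seen the other way round, incomplete response was 37/237 = 15.6% with low and 32/278 = 11.5% with high willingness.

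The data are compatible with no association and with a large one. Table 3 also pools the three arms, and Table 4 compares arms at baseline only, so neither shows whether dropout differed by arm.

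**4. Illustration of possible bias (assumed inputs)**

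Dropout by arm is not reported. Suppose 23 of the 69 fall in one arm of 172, and that their day-7 willingness would differ from that of completers by 10 to 30 points, in that arm only. Excluding them shifts the arm contrast by 0.10 × 23/172 = 1.3 points to 0.30 × 23/172 = 4.0 points. With 13 to 33 dropouts in that arm, the range widens to 0.8 (0.10 × 13/172) to 5.8 points (0.30 × 33/172). This shows scale only; nothing in the article shows that such a bias exists.

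**The case against.** The strongest reply is one of placement. The sentence is under Subanalyses, inside the path-analysis paragraph, directly after a sentence about path-model estimates. The main analysis has its own section and its own population, and mixed models can keep people with partial follow-up. The efficacy section is coherent without the exclusion rule, and the analytic 450 can be read as allowing for dropout without defining an analysis set. This stands as far as it goes: removal from the primary analysis is one reading, not a stated fact. It does not dispose of the point, because the sentence is unrestricted as written and the narrow reading still leaves a complete-case mediation analysis.

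Three stronger readings are tempting, and the documents do not support them.

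- A reader might infer that exclusion is justified by the non-significant attrition comparison. The Results report that comparison and stop; they do not give it as a reason for excluding anyone.
- A reader might infer that dropout is related to baseline willingness. The interval includes zero (P = .17), and a non-significant gap cannot be taken as established any more than it can be taken as absent.
- A reader might make much of 446 falling below 450. That is four people and carries no weight.

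It is also fair to say that model covariates and sensitivity analyses are commonly left to the analysis plan, and their absence is not criticised here. The point concerns a rule that the article does state.

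**Conclusion.** The point holds in a limited form. The article states an exclusion rule without a scope, and as worded the rule conflicts with the intention-to-treat population set one section earlier. The loss is at most 69 of 515 (13.4%), with standard errors at most about 7.5% larger, on the assumption that any missing survey triggers exclusion and that Table 3's 446 is the correct count. If the rule is confined to the path analysis, the efficacy analysis is untouched, but the mediation results rest on a different population.

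Bias in the arm contrast is possible but not shown. Table 3 neither demonstrates it nor rules it out, given its low power and the pooling of arms. This should be fixed before analysis; it does not undermine the design.

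**What to change.** Replace the exclusion sentence with text to this effect: the mixed-effects models use every available survey from all 515 randomised participants and are fitted by maximum likelihood; the path models use full-information maximum likelihood on the same participants; a complete-case path analysis is reported only as a sensitivity analysis. State that these methods assume missingness depends only on observed data. Report the number of incomplete responders by arm and by survey.

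If the authors prefer to keep a complete-case path analysis, the minimum is one clause limiting the rule to it, with the number analysed given beside the efficacy results. A sensitivity analysis that shifts missing day-7 intention, and showing Table 3 as differences with confidence intervals, would be useful but are optional.

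The cost is a few lines of wording and a little programming in software the article already names. No new data are needed. Collection has ended, so the clarification should be dated and recorded before the analysts learn which coded group is which.

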## Methods

### Study Design

A randomized controlled trial (RCT) will be conducted and reported according to the CONSORT-EHEALTH (Consolidated Standards of Reporting Trials of Electronic and Mobile Health Applications and Online Telehealth) checklist, and the protocol timeline is shown in Table 1. This study is a 3-arm prospective RCT enrolling >450 participants with underlying medical conditions (Figure 1). The participants who complete their baseline web-based questionnaire will be recruited into the study and randomly assigned to 3 equal groups, stratified by their underlying disease, sex, age, and willingness to receive a COVID-19 vaccine (willingness and hesitation). The participants will be randomized to receive (1) standard information about COVID-19 vaccination (control group), (2) COVID-19 vaccination DA (intervention group *SMART-DA*), or (3) COVID-19 vaccination DA with targeted information provision (intervention group *SMART-DA*-α). Each group is described in detail in the following sections. After 1 week, we will follow-up with the participants and use an intention-to-treat (ITT) approach to determine the effects of their COVID-19 communication intervention on COVID-19 vaccination. There is no expected harms or unintended effects in each group.

**Table 1 table1:** Spirit figure protocol timeline.

			Enrollment		Pretreatment assessment		Allocation		Postallocation assessment				Close out
Time point			-t_1_		0		0		t_1_		t_2_		t_3_

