#### Primary and Secondary Outcomes

The primary and secondary outcomes and potential mediators are listed in Table 2. Our primary outcome is COVID-19 vaccination intention, which will be an important outcome during the 1-week follow-up period. The baseline, posttest (3-day), and follow-up (1-week) surveys will assess the participants’ vaccination intention. A 5-point Likert scale questionnaire will measure the intention to be vaccinated against COVID-19. The participants will be asked, “If a vaccine for Coronavirus (COVID-19) becomes available, would you want to receive it?” and provided the response options “1=Definitely Would Not Want It, 2=Would Likely Not Want It, 3=Neutral or Unsure, 4=Would Likely Want It, and 5=Definitely Would Want It.” The level of vaccine acceptance is defined as willing (“Definitely Would Not Want It,” and “Definitely Would Want It”) or hesitant (“Definitely Would Not Want It,” “Would Likely Not Want It,” and “Neutral or Unsure”). The secondary outcomes include knowledge level related to COVID-19, which will be assessed using a validated questionnaire that has been used in numerous studies [34,35], and decisional conflict, which will be assessed using the decisional conflict scale [36]. In addition, psychological stress owing to decision-making regarding COVID-19 vaccination will be measured.

**Table 2 table2:** Study outcome measures.

			Baseline measurement (day 1)		Posttest measurement (day 3)		Follow-up measurement (day 7)

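### The subgroup analysis by baseline intention names change within the willing and hesitant groups, with no control comparison or interaction; read as pre-post change, it would carry regression to the mean

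*Protocol article*

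**What the plan says.** The primary outcome and the subgrouping variable are the same measure. Under Primary and Secondary Outcomes, "Our primary outcome is COVID-19 vaccination intention", and "A 5-point Likert scale questionnaire will measure the intention to be vaccinated against COVID-19", at baseline, day 3 and day 7. Under Subanalyses, "we will conduct subgroup analyses according to the preintervention intent for vaccination". The quantity to be examined is then named: "We will observe how the degree of vaccination intention changes in the 2 groups". As the trial has three arms, the two groups are most naturally the baseline willing and hesitant participants. The paragraph closes with a causal aim for those already willing at baseline: "we seek to identify whether the nature of their decisions changes through the intervention".

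The paragraph mentions neither the control arm nor an arm-by-subgroup interaction. Elsewhere the design supplies what such a comparison needs. Under Study Design, participants are "randomly assigned to 3 equal groups, stratified by their underlying disease, sex, age, and willingness to receive a COVID-19 vaccine", and one arm receives standard information. Evaluation of Efficacy estimates intervention effects with mixed-effects models.

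**The concern.** When people are selected on a noisy score and the same score is followed, those selected low tend to rise and those selected high tend to fall, whatever is done to them. Vaccination intention here is a single item on a five-point scale, so some instability between surveys is to be expected.

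If the planned observation is change from baseline within each group, a rise among the hesitant and a fall among the willing could be read as the aid persuading the hesitant and unsettling the willing. An aid with no effect would produce the same pattern.

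A smaller issue concerns the last aim. The paragraph worries that some willing participants decided passively or under social or economic pressure, and asks whether the nature of their decisions changes. The only measure named there is the degree of intention. That item asks whether the person would want the vaccine, not whether the choice was voluntary, and someone who starts at 5 cannot score higher.

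**Working it through.** **Inputs from the protocol.** The Results section and Table 4 give 237 of 515 hesitant and 278 of 515 willing. By arm (SMART-DA, SMART-DA-α, control) these are 79, 80, 78 hesitant and 93, 92, 93 willing. Check: 237/515 = 46.0% and 278/515 = 54.0%; 79 + 80 + 78 = 237 and 93 + 92 + 93 = 278. The stated split is reproduced.

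**Assumptions not in the protocol.** Test-retest correlation r of intention over the follow-up, taken as 0.5 to 0.9. A bivariate normal latent score with equal variance at both times, no intervention effect and no general drift. For results in scale points, a spread over the five categories of 8/14/24/34/20%, chosen to match the 46/54 split.

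**Step 1: mean baseline position of each group.** The cut c is the 46th percentile of a standard normal. The means are -φ(c)/0.46 = -0.863 SD (hesitant) and +φ(c)/0.54 = +0.735 SD (willing).

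**Step 2: expected change with no effect.** The expected follow-up score is r times the baseline score, so the expected change is -(1 - r) × baseline mean.

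| r | Hesitant (latent SD) | Willing (latent SD) |
|---|---|---|
| 0.9 | 0.1 × 0.863 = +0.09 | -0.1 × 0.735 = -0.07 |
| 0.7 | 0.3 × 0.863 = +0.26 | -0.3 × 0.735 = -0.22 |
| 0.5 | 0.5 × 0.863 = +0.43 | -0.5 × 0.735 = -0.37 |

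**Step 3: the same on the five-point item (simulation, no effect).** The last column is the share of trials in which a two-sided paired t test at 0.05 rejects in one arm's hesitant stratum (n = 79).

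| r | Hesitant change (points) | Willing change (points) | Hesitant who cross to willing | Paired test rejects |
|---|---|---|---|---|
| 0.9 | +0.17 | -0.14 | 16% | 53% |
| 0.7 | +0.39 | -0.33 | 27% | 90% |
| 0.5 | +0.60 | -0.51 | 36% | 99% |

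**Step 4: the randomized contrast in the same simulated data.** Comparing two arms within a stratum (79 versus 79 hesitant, 93 versus 93 willing) gives a mean difference in change between -0.008 and +0.002 points. The two-sided type I error is 4.6% to 5.3% across the r values tried. The regression to the mean is the same in each arm and cancels.

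**The case against.** The strongest reply is that the control arm has not been set aside. The paragraph speaks of subgroup analyses, follows an efficacy section built on mixed models of intervention effects, and asks about change through the intervention. In a randomized trial the ordinary reading would be that the effect analysis is repeated by baseline willingness. Allocation is stratified by willingness, and Table 4 shows near-identical splits across arms (P = .99). Contrasts and interaction terms are often left to an analysis plan, and a journal article condenses further.

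Much of this stands. The sponsor may well intend a comparison between arms, and step 4 shows that it would be sound. The paragraph is not merely silent, however. It names a quantity, change within two groups formed on the outcome, and attaches a causal aim to it. That named quantity is what needs correcting.

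Three stronger readings are tempting and are not supported:
- A reader might infer that subgrouping on the baseline outcome is itself biased. It is not: baseline intention is measured before randomization and is a stratification factor.
- A reader might infer that the trial will report a false effect in the hesitant. The paragraph speaks only of observing change and states no test or decision rule.
- A reader might set the shifts above against the effect size of 0.2 under Sample Size and Power. The protocol does not say that 0.2 is in standard deviation units, so the two cannot be compared.

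Nor does the protocol say that the intention score is the sole measure for the nature of decisions; it simply names no other there.

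**Conclusion.** The point holds conditionally. If the sentence is followed literally as pre-post change within each subgroup, regression to the mean would push the hesitant up and the willing down with no true effect, by 0.09 to 0.43 and 0.07 to 0.37 latent SD respectively for r from 0.9 down to 0.5. The direction needs only an imperfect correlation between surveys. The size depends on r, which the protocol does not give, and the results in scale points also depend on the assumed spread over categories. If arms are compared within each stratum, the problem disappears.

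This concerns a secondary analysis and leaves the main efficacy analysis untouched. It is still worth correcting, because the valid comparison is available and the text does not state it.

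**What to change.** Replace the sentence on observing change in the two groups with text to this effect: within the willing stratum (baseline score 4-5) and the hesitant stratum (baseline score 1-3), the difference between each decision-aid arm and control at day 7 will be estimated from the primary mixed model with an arm-by-baseline-intention (by time) interaction. The interaction will be reported with its confidence interval as exploratory, and no conclusion about the intervention will be drawn from pre-post change within a subgroup.

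Give the strata as scores. The definition under Primary and Secondary Outcomes lists the lowest response category under both willing and hesitant and omits category 4, so the 4-5 and 1-3 split is the apparent intent and should be confirmed.

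Optionally, name the decisional conflict and stress scores, already collected at all three surveys, as the measures for the nature-of-decisions question. They come closer to it than the intention item does.

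The cost is wording and one added interaction, with no new data. The drawback is limited power. With the baseline counts and a common SD s, the SMART-DA versus control contrast has standard error s × √(1/172 + 1/171) = 0.108s overall. The difference of that contrast between strata has s × √(1/79 + 1/78 + 1/93 + 1/93) = 0.217s, about twice as large. A non-significant interaction should therefore not be read as evidence of equal effects.

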##### Description of SMART-DA

The *SMART-DA* follows a stepwise approach and encourages decisions consistent with the participant’s values and health condition. The *SMART-DA* consists of five steps: (1) clarify the decision; (2) explore the decision in terms of knowledge, values, and certainty; (3) clarify decisional support; (4) identify the decision-making needs; and (5) plan the next steps based on the needs.

Step 1 consisted of 4 questions that required the participants to consider the key decision. The following questions were addressed: (1) “What options are available when deciding to be vaccinated against COVID-19?” (2) “What is making your COVID-19 vaccination decisions difficult?” (3) “When do you think it is time to make a COVID-19 vaccination decision?” and (4) “How far have you reached the final decision on the COVID-19 vaccination?” Multiple options were provided to increase the participants’ convenience. For question 1, we provided 3 options for COVID-19 vaccination decision-making: “Get vaccinated as soon as possible,” “Delay vaccination as much as possible,” and “Refuse vaccination.” If necessary, they could write their responses in the “other” column.

In step 2, the participants explored their knowledge and values related to each option to clarify how certain they were in their decision-making. A list of reasons to choose and not to choose each option (eg, “Get vaccinated as soon as possible,” “Delay vaccination as much as possible,” and “Refuse vaccination”) was provided, and the participants rated how much each reason mattered to them using a 6-point Likert-type scale. If necessary, they could write their reasons in the “other” column and rate how much they mattered. After the rating was completed, the total score for choosing each option and the reasons for not choosing it were calculated and shown. The participants were then asked what their preferred options were.

In step 3, the participants were asked to think about who supports their decision-making and how the support affects them. We asked them to identify whether other people supported their decision-making and, if so, who those individuals were. In addition, we asked them what role they preferred to play in decision-making and provided the response options “share the decision,” “decide myself after hearing views,” and “someone else decides.”

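### The subgroup question about the nature of willing participants' decisions is paired only with change in the 1-5 intention score, which cannot answer it

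*Protocol article*

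**What the plan says.** The Subanalyses section plans subgroup analyses by vaccination intent before the intervention and names one quantity for them: "We will observe how the degree of vaccination intention changes in the 2 groups". It then explains its interest in the willing group, saying that "there are cases in which their decisions are passive or involuntary owing to social pressure or economic activity", and draws the aim from this: "we seek to identify whether the nature of their decisions changes through the intervention".

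The section on Primary and Secondary Outcomes defines the measure: "A 5-point Likert scale questionnaire will measure the intention to be vaccinated against COVID-19". The item asks whether the person would want a vaccine, and its top two options are "4=Would Likely Want It, and 5=Definitely Would Want It". The same section gives the rule for the subgroups: "The level of vaccine acceptance is defined as willing (“Definitely Would Not Want It,” and “Definitely Would Want It".

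Tables 1 and 2 list six outcomes at baseline, day 3 and day 7: intention, knowledge, decisional conflict, stress related to vaccination, perceived benefits and perceived barriers. None is described as measuring voluntariness or social pressure.

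The nearest content is in step 3 of the decision aid, where "participants were asked to think about who supports their decision-making and how the support affects them" and state which role they prefer in the decision. That is part of the intervention, and the control group receives only standard public information.

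**The concern.** The aim is about the kind of decision a willing person has made. The named quantity is how strongly that person wants the vaccine. These are different constructs, and the second does not reveal the first.

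Two misreadings follow. A flat intention score among willing participants could be reported as showing that the nature of their decisions did not change, although that was not measured. A falling score could be reported as harm, although it might come from a participant who felt pressed to agree and became more candid after using the decision aid. The article presents the tool as support for informed decision-making, so either misreading would bear on how the tool is judged in the willing group.

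**Working it through.** **1. Aim against measure.** The table uses invented participants, for illustration only.

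| Before | After | Change in intention | Change in nature of decision |
|---|---|---|---|
| 5, under pressure | 5, freely chosen | 0 | yes |
| 5, freely chosen | 5, freely chosen | 0 | no |
| 5, under pressure | 3, freely stated doubt | -2 | yes |
| 5, freely chosen | 3, new doubt | -2 | no |

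The same score change occurs with and without a change in the nature of the decision. Intention change therefore does not identify the quantity in the aim, whatever the sample size.

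**2. Size of the group.** The Results text gives 278/515 with high intention, and Table 4 gives 93, 92 and 93 by arm. 93 + 92 + 93 = 278, and 278/515 = 0.5398, or 54.0%. The text prints 53.9% and Table 4 prints 54%, so the figure reproduces apart from rounding.

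**3. Upward room on the scale.** Assume that willing means answers 4 and 5. Room to rise is 5 - 4 = 1 point from answer 4 and 5 - 5 = 0 from answer 5. Let p be the share of the willing group answering 5, which the article does not report. The number at the maximum is 278p, the number able to rise is 278(1 - p), the largest possible mean rise is (1 - p) points, and the share of all participants at the maximum is 278p/515.

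| p (assumed) | At 5 | Able to rise | Largest mean rise | Share of 515 at maximum |
|---|---|---|---|---|
| 20% | 56 | 222 | 0.8 | 10.8% |
| 40% | 111 | 167 | 0.6 | 21.6% |
| 60% | 167 | 111 | 0.4 | 32.4% |
| 80% | 222 | 56 | 0.2 | 43.2% |
| 100% | 278 | 0 | 0 | 54.0% |

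More than half of the whole sample would be at the maximum only if p exceeded 0.5 x 515/278 = 0.926. Upward movement is thus limited to 1 point, while a participant starting at 4 or 5 can fall by 3 or 4 points.

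**4. The definition of willing.** As printed, willing consists of answers 1 and 5, and hesitant consists of answers 1, 2 and 3. Answer 1 falls in both groups and answer 4 in neither. The intended rule is apparently 4 and 5. Step 3 depends on that reading; step 1 does not.

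**5. What else is available.** Decisional conflict and stress are scheduled for all arms at all three surveys, and the Evaluation of Efficacy section already plans models for both. The Subanalyses section does not link either of them to this aim. The decision-aid questions on support and preferred role have no control-arm counterpart, so they cannot give a randomised comparison.

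**The case against.** The strongest reply is that the sentence stating the aim names no variable, and the intention sentence stands two sentences before it. Nothing forbids using decisional conflict or stress, and the choice of outcome for a secondary subgroup question is often left to the analysis plan. This is fair in part. The article does not rule out another outcome. But it does more than leave the outcome open: one short paragraph names a single quantity and then draws this aim from its discussion of the same subgroup. A reader following the text would analyse intention.

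It can also be said that the items of the decisional conflict and stress measures are not reproduced, so they might touch on pressure or free choice. That stands. The documents show only that no outcome is described as measuring voluntariness.

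Two stronger readings are tempting and are not supported. A reader might infer that the willing group is at the ceiling of the scale. The split between answers 4 and 5 is not given, answer 4 can rise, and every score in the group can fall. A reader might also infer that over half of the sample cannot inform the aim. The limit lies in the measure, not in the 278 participants, who are also scheduled to give decisional conflict and stress data and who contribute to the main analysis.

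Finally, this is a subanalysis: the primary outcome, main model and sample size are untouched. That is correct and limits the weight of the point.

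**Conclusion.** The point holds in a limited form. Change in the 1-5 intention score cannot show whether willing participants' decisions became less passive or involuntary, because pressured and free willingness can score alike. This rests on the wording of the item and needs no numerical assumption.

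The limited upward room is a secondary difficulty: at most 1 point in a group of 278/515 (54.0%), assuming that willing means answers 4 and 5. The mean room is between 0 and 1 point, depending on the unreported split. A null result is not guaranteed, since scores can fall; but neither a flat nor a falling score answers the stated question.

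This is a secondary aim that should be repaired before its result is interpreted. It does not threaten the primary comparison.

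**What to change.** - Correct the definition of willing in Primary and Secondary Outcomes so that each of the five answers belongs to exactly one group, and form the subgroups only after that.
- Keep change in intention as the stated comparison in both the willing and the hesitant subgroup.
- For the aim on the nature of decisions, name decisional conflict as the outcome in the willing subgroup, supported by decision-related stress. Compare each intervention arm with control using the baseline, day 3 and day 7 data.
- State that both are indirect measures of voluntariness, and that neither a flat nor a falling intention score will be interpreted as evidence on it.
- If this is not adopted, restate the aim as change in intention and drop the claim about the nature of decisions.

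The cost is wording and one additional subgroup model for each of two outcomes already scheduled. The small downside is that the measures are indirect. A new survey question on pressure is not an option, because data collection ended in January 2022. The article says that it was initially submitted before data analysis began. If results by arm have been seen since then, the added analysis should be reported as post hoc.
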